### Delirium outcomes

The incidence of delirium will be diagnosed with the Confusion Assessment Method (CAM) [27], whereas the duration (number of days) and severity of the delirium will be assessed using the Delirium Rating Scale (DRS-R) [34]. In patients who fulfill the selection criteria, ward nurses will rate delirious symptoms daily using the Delirium Observation Scale (DOS) [35] at the end of each shift until discharge. This approach is already part of standard clinical practice and the VMS. When the patients receive a positive score for the DOS, the CAM will be administered by the nurse practitioner or geriatrician. In patients diagnosed with delirium according to the CAM, the Delirium Rating Scale (DRS-R) [34] will be administered daily by the nurse practitioner.

#### The confusion assessment method (CAM)

The CAM, a 4-item diagnostic instrument, was designed as a screening tool for people who are at high risk of delirium [27] and is seen as the gold standard in most delirium studies [30].

The CAM assesses the presence of four delirium features: acute onset and fluctuating course, inattention and distractibility, disorganized thinking and illogical or unclear ideas, and an alteration in consciousness. A review concluded that the CAM has become widely used, mainly because of its ease of use and accuracy [36,37]. The overall sensitivity appeared to be 94% and the specificity 89%; interrater reliability was high (0.70-1.00). In addition, the CAM has been translated into over 15 languages, including Dutch [36].

#### The delirium observation scale (DOS)

The DOS was developed to facilitate early recognition of delirium, based on nurses' observations during regular care; this scale uses DSM-IV criteria for delirium, a literature review, and clinical experiences [35]. This measure consists of 13 items that are rated on a 3-point scale based on the frequency of occurrence of the behavioral change, including never (0 points), sometimes–always (1) or do not know (−). A total score of three or higher is indicative of being delirious [35]. The DOS scale was determined to be valid and showed high internal consistency. Predictive validity against the Diagnostic and Statistical Manual-IV diagnosis of delirium made by a geriatrician was good [30]. The DOS had reported sensitivities of 0.89 and 0.94 and specificities of 0.77 and 0.88 [38].

#### The delirium rating scale (DRS-R)

The Delirium Rating Scale was developed in 1988 and revised in 1998 [34]. This scale was originally designed to be used by psychiatrists but can also be used by other physicians, nurses and psychologists with appropriate training. The DRS-R-98 is a 16-item clinician-rated instrument with 13 severity items and 3 diagnostic items. The maximum total score is 46 points, and the maximum severity score is 39 points [34]. To rate the items on the DRS, all sources that are available are used (e.g., nurses, family and medical files) [34]. Interrater reliability (ICC = 0.98) and internal consistency were very high, and the sensitivity and specificity were 92% and 93%, respectively [34].

### Quality of life outcomes

Health related quality of life (general quality of life, functional wellbeing and emotional wellbeing) will be measured with the EQ-5D [39] at baseline (admission to the hospital) and at discharge from the hospital. The EQ-5D is a multidimensional measurement of health consisting of the EQ-5D descriptive system and the EQ VAS. The EQ VAS records the respondents self-rated health status on a vertical graduated (0–100) visual analogue scale. The EQ-5D descriptive system comprises 5 dimensions of health (mobility, self-care, usual activities, pain/discomfort and anxiety/depression).

Each dimension comprises three levels (no problems, some/moderate problems or extreme problems). The EQ-5D may be used to calculate quality adjusted life years (QALYs).

Test-retest reliability has been shown to be good, and the test is easy to use to measure both the presence of clinical symptoms and changes in these symptoms over time [39].

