### Cost-effectiveness outcomes

The primary effect parameter of the economic outcome evaluation will be the number of prevented cases of delirium. The costs of the HELP program will be calculated as well as the costs of care consumption of both patients who received HELP and patients who did not both during and after their hospital stay. After discharge, the patients will be contacted three times by telephone during a period of three months for assessment of their care consumption. During this telephone call, patients will be asked eight short questions addressing the following topics: possible hospital (re)admissions, nursing home or rehabilitation center admissions, home care, domestic help, informal care, visits from the general physician and psychological care. If the patients are not able to participate, a close family member will be asked for information on the care that the patients have received after discharge. Differences in total cost between the intervention and control groups will be compared.

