### Costs-evaluation

Differences in total mean costs between groups will be related to the differences in the number of cases of delirium and of the QALYs gained after three months. QALYs will be calculated by multiplying the utility of a health situation by the time spent in these health situations. The incremental cost effectiveness ratio (ICER) will be calculated and graphically presented as a scatter of bootstrapped ICERs on the cost-effectiveness plane and as an acceptability curve for a series of willingness to pay ceilings. Sensitivity analyses will be conducted that will focus on the most salient cost-drivers.

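### The three-month cost-per-QALY ratio has no described utility measurement after hospital discharge, so it would rest mainly on an unstated extrapolation

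*Protocol article*

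**What the plan says.** Three sections of the Protocol article bear on this point.

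- **Quality of life outcomes** gives the measurement times. Health-related quality of life "will be measured with the EQ-5D [39] at baseline (admission to the hospital) and at discharge from the hospital". The same section names the EQ-5D as the instrument from which QALYs may be calculated. No other utility instrument appears in the article.
- **Cost-effectiveness outcomes** describes the contact after discharge: "patients will be contacted three times by telephone during a period of three months for assessment of their care consumption". The calls consist of eight short questions, on these topics: "possible hospital (re)admissions, nursing home or rehabilitation center admissions, home care, domestic help, informal care, visits from the general physician and psychological care". The section also makes prevented delirium cases the primary effect measure of the economic evaluation.
- **Costs-evaluation** gives the horizon and the method. Differences in mean total costs are to be "related to the differences in the number of cases of delirium and of the QALYs gained after three months", and "QALYs will be calculated by multiplying the utility of a health situation by the time spent in these health situations". Bootstrapped ICERs on the cost-effectiveness plane and an acceptability curve are to follow, with sensitivity analyses directed at the main cost drivers.

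**The concern.** A QALY over three months needs a utility for each part of those three months. As described, the last utility is recorded on the day the patient leaves hospital. Everything later has to be supplied by a rule, and the article states none: no carry-forward, no mapping from care use, no assigned values for health states.

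The gap cannot be closed at the analysis stage. An analysis plan can choose an extrapolation rule but cannot create observations. The multiple imputation named under Statistical analysis does not help either, because utility after discharge would be missing for every patient and there would be no observed values to impute from.

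The unmeasured period also matters for the question asked. The Background says that delirium can bring lasting functional limitations, persistent cognitive decline and loss of quality of life after hospitalization. A benefit of prevention that appears only after discharge would not be seen.

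Finally, the bootstrap resamples patients, and every resample would apply the same extrapolation rule. The scatter and the acceptability curve for QALYs would show sampling error only and so look more certain than they are.

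**Working it through.** The article states no QALY figure, utility difference or length of stay, so there is no figure of its own to reproduce. The check compares the measurement schedule with the horizon.

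**Inputs**
- EQ-5D times: admission and discharge (Quality of life outcomes).
- Horizon: three months, taken as 91.3 days (Costs-evaluation). The article does not say whether this runs from admission or discharge, so both are shown.
- Length of stay L: 5, 7, 10, 14 and 21 days. This is an assumption.

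**Share of the horizon after the last EQ-5D**
- Three months counted from discharge, horizon L + 91.3: share = 91.3 / (91.3 + L).
- Three months counted from admission: share = (91.3 − L) / 91.3.

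| L (days) | From discharge | From admission |
|---|---|---|
| 5 | 91.3/96.3 = 94.8% | 86.3/91.3 = 94.5% |
| 7 | 91.3/98.3 = 92.9% | 84.3/91.3 = 92.3% |
| 10 | 91.3/101.3 = 90.1% | 81.3/91.3 = 89.0% |
| 14 | 91.3/105.3 = 86.7% | 77.3/91.3 = 84.7% |
| 21 | 91.3/112.3 = 81.3% | 70.3/91.3 = 77.0% |

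The range is about 77% to 95%. With an EQ-5D at a call at the end of the three months, the share after the last measurement would be 0%.

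**What the unmeasured part can contribute.** The utility differences d between groups are assumed, and 0.25 year after discharge is used.
- Difference d at discharge that stays constant: d × 0.25. For d = 0.05 this is 0.0125 QALY.
- Difference d at discharge that fades linearly to zero: 0.5 × d × 0.25. For d = 0.05 this is 0.00625 QALY.
- No difference at discharge, opening linearly to d at three months: 0.5 × d × 0.25. For d = 0.05 this is 0.00625 QALY. The described schedule would record none of it.
- For d = 0.02 and d = 0.10, the constant case gives 0.005 and 0.025, and each of the two linear cases gives 0.0025 and 0.0125.

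**What the measured part can contribute.** If a difference of 0.05 builds up linearly between admission and discharge, the in-hospital part is 0.5 × 0.05 × L/365.25. That is 0.0005 QALY for 7 days and 0.0010 for 14 days. In these examples the measured part is small against every non-zero value assumed for the period after discharge.

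**The case against.** Several objections deserve weight.

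- **QALYs are not the primary economic measure.** This stands. Cost per delirium case prevented needs no utility, and neither do the comparison of costs or the analysis of delirium incidence. A reader might infer that the cost-effectiveness aim as a whole fails. The article does not support that.
- **Not all of the article is visible.** Figure 1, the overview of measurements, is not shown. The Abstract's list of secondary outcomes could be read loosely so that its three-month phrase covers quality of life. This justifies saying that no later measurement is described, rather than that none exists. It does not remove the point: the section on quality of life states the two times in plain words, and the Abstract's phrase attaches most naturally to the use of care services. One of the eight telephone questions may not be spelled out, but a single question cannot hold the five EQ-5D dimensions.
- **The plan does not say that the discharge value will be carried forward.** This stands. Utility multiplied by time in a health situation could also mean assigned utilities for states reconstructed from the calls, such as home or nursing home. That too would be an extrapolation from values not measured in these patients, and it is not stated.
- **The QALY amounts are illustrations.** This stands. A reader might infer that the ICER denominator will be wrong by a factor of two. The factor is only a constant difference set against one that fades linearly to zero. A difference that persists gives no such error, and one that widens gives an error in the other direction. Nor does any passage show that patients are still delirious when the discharge EQ-5D is taken.

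**Conclusion.** The schedule and the horizon do not fit together. As described, a three-month QALY would be observed for the hospital stay and assumed for the rest in every patient. The assumed part is about 77% to 95% of the horizon, given stays of 5 to 21 days; it is the majority under either starting point for the three months. The direction and size of any resulting error in the cost-per-QALY ratio cannot be determined from the article.

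The consequence is confined to the cost-per-QALY ratio, its bootstrap plane and its acceptability curve. This is a should-fix point: it concerns one secondary economic result, but it cannot be repaired once the follow-up calls have been made.

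**What to change.** **Preferred change.** Add the EQ-5D descriptive system to the planned calls, at least to one placed at three months, with a proxy version where a family member answers. Compute QALYs as the area under the utility curve from admission to three months, with utility 0 from death, and state from which day the three months run. The descriptive system is enough for utilities; the EQ VAS is a visual scale and need not be put on the telephone.

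**Cost.** A protocol amendment and a few extra minutes per call, in a frail population where the Discussion already names participation as a concern. A single EQ-5D at three months keeps this small; using all three calls traces recovery better. The change should be in place from the start: in a stepped-wedge trial, a late addition would leave the unmeasured patients concentrated in the control periods.

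**If the calls cannot be changed.** Either limit QALYs to the period between admission and discharge, or label the three-month cost per QALY as a model-based extrapolation. In the second case, state the rule and vary utility after discharge in sensitivity analyses, alongside the cost drivers already planned. Under either option, base the economic conclusion on cost per delirium case prevented.

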### Qualitative outcomes

The quality of care will be examined by means of focus groups. The quality of the care “process” experienced by the patients will be studied at each of the participating units during the period of data collection. Focus group meetings will be held with the multidisciplinary HELP-team. These focus groups will be led by a qualitative researcher with the assistance of the HELP-trained professionals and research-project members. The HELP program, care pathways, and the cooperation within the multidisciplinary team are topics that will be discussed by these focus groups. Next, qualitative interviews with the patients and their family members will be conducted. The objective of these interviews is to collect information on the experiences and opinions about the HELP program from both the patients and their next of kin.

Furthermore, the HELP volunteers will participate in a so called focus group to evaluate their role and experiences; each unit will have one group that participate every month during the first half year and then every two months during the period of data collection.

### Cost-effectiveness outcomes

The primary effect parameter of the economic outcome evaluation will be the number of prevented cases of delirium. The costs of the HELP program will be calculated as well as the costs of care consumption of both patients who received HELP and patients who did not both during and after their hospital stay. After discharge, the patients will be contacted three times by telephone during a period of three months for assessment of their care consumption. During this telephone call, patients will be asked eight short questions addressing the following topics: possible hospital (re)admissions, nursing home or rehabilitation center admissions, home care, domestic help, informal care, visits from the general physician and psychological care. If the patients are not able to participate, a close family member will be asked for information on the care that the patients have received after discharge. Differences in total cost between the intervention and control groups will be compared.

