## Background

In the next 30 years, the proportion of people 65 years and older is expected to increase to account for 25% of the general Dutch population, compared to 15% in 2008 [1]. Older people are at a higher risk for hospitalization. Of every 10,000 people 65 years and older, 3,131 older people were admitted to the hospital in 1995 and 5,521 in 2010 [2]. In 2005, 25 % of the admitted patients in hospitals were 70 years old or older, for totaling 400,000 people [3]. The risk for delirium is significantly associated with age, and in 2005, the Dutch Health Care Inspectorate (IGZ) indicated that 40,000 to 160,000 hospitalized patients 70 years and older suffer from delirium annually in the Netherlands [3].

Delirium is characterized by an acute disruption of attention and cognition [4] and is the main cause of confusion in the general hospital [5]. The DMS-IV criteria for delirium are as follows: a disturbance of consciousness with a reduced ability to focus, sustain, or shift attention; a change in cognition (memory, language, or orientation) or the development of a perceptual disturbance not related to dementia; a quick onset that fluctuates during the day; and an underlying physiological problem or medication as the cause [4].

Patients with delirium are at an increased risk for complications and mortality during a hospital stay. Delirium can further result in adverse events after hospitalization, including lasting functional limitations, persistent cognitive decline, loss of quality of life for the patient and family, re-hospitalization and nursing home admission [6-8]. Unfortunately, nurses and physicians often do not recognize the presence of delirium [5]. Once delirium is diagnosed, standard delirium treatment consists of diagnosis and treatment of the underlying medical condition. Furthermore, management of delirium consists of environmental interventions addressing orientation, day structure, safety and, if necessary, the prescription of (antipsychotic) drugs [5].

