### Study population

Eligible participants are patients ages 70 years and older who are at risk for delirium and are admitted to the cardiology, internal medicine, geriatrics, orthopedics and surgery units of the two hospitals. The Diakonessenhuis is situated in two locations (one in a university city and one in a smaller town nearby), while the Hospital Gelderse Vallei is located in a more rural area.

Eligible patients will be approached by the nurse on call for participation within 24-hours after hospital admission. Inclusion criteria are being 70 years and older, the absence of delirium at hospital admission and being considered at risk for delirium.

To assess whether a patient is at risk for delirium, we use the three questions of the Hospital Safety Program launched in the Netherlands in 2009 that are part of obligatory hospital care. A review of literature was done before choosing these questions [26]. The nurse will assess the risk for delirium in patients 70 years and older with the following questions: “Do you have memory problems?”; “During the past 24-hours, did you need assistance with your daily self-care?”; and “Were you confused during earlier hospital admissions or illnesses?”. When at least one of these questions is answered positively, there is an increased risk of delirium.

Exclusion criteria include a life threatening situation, being in a palliative phase at admission, an expected hospital stay of 24 hours or less, being legally incapable of participating, unable to communicate verbally, or a second hospital admission during the study period. If the patients are transferred to a participating unit, they are treated as a newly admitted patient; if the patients are transferred from a participating unit to a nonparticipating unit, they are excluded from the study.

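### All post-discharge care use, readmissions included, comes from telephone report by patients who may have been enrolled for memory problems; the cost difference may be distorted, with uncertain size and sign, and readmissions to the two hospitals could be taken from records

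*Protocol article*

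**What the plan says.** The source of the data is in the protocol article under Cost-effectiveness outcomes. After discharge "the patients will be contacted three times by telephone during a period of three months for assessment of their care consumption". At each call "patients will be asked eight short questions addressing the following topics"; the topics are readmission, nursing home or rehabilitation stays, home care, domestic help, informal care, general physician visits and psychological care. The rule for a substitute informant is: "If the patients are not able to participate, a close family member will be asked for information on the care" received. The article gives no criterion for being unable to take part and mentions no check against records. The results feed the comparison: "Differences in total cost between the intervention and control groups will be compared".

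Two other sections bear on who is being asked.

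- Study population: one of the three risk questions is "Do you have memory problems", and one positive answer is enough ("When at least one of these questions is answered positively, there is an increased risk of delirium"). The exclusions include "being legally incapable of participating, unable to communicate verbally, or a second hospital admission during the study period".
- Background: possible consequences of delirium are listed as "lasting functional limitations, persistent cognitive decline, loss of quality of life for the patient and family, re-hospitalization and nursing home admission".

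**The concern.** A patient who can hold a short telephone conversation but cannot recall the past weeks of care does not meet the condition for asking the family. That patient remains the informant, and whatever is forgotten is recorded as care not used. By the article's own account, the patients likely to use most care after discharge include those whose cognition may have suffered most.

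Cost-effectiveness is part of the primary aim, and the Conclusion makes national implementation depend on it. Post-discharge cost enters both the total cost difference and the ICER. Nothing planned would detect or repair misreporting:

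- Multiple imputation (Statistical analysis) deals with missing answers, not with wrong ones.
- Sensitivity analyses on the main cost drivers (Costs-evaluation) cannot separate recall error from true use unless the informant is known or a record check exists.

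**Working it through.** The article states no figure for recall error, family response or cost by delirium status, so there is nothing to reproduce. The check asks what sign and size the error could have.

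**Inputs**

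- Difference in delirium incidence, d = 0.10 (Sample size).
- Post-discharge cost: 1 without delirium and R with delirium. Assumed, R = 1.5, 2 or 3.
- Proportion of post-discharge cost not reported: u0 without delirium, u1 with delirium. Assumed, 0 to 40%.
- Simplifications: HELP changes post-discharge cost only through the number of delirium cases, and u0 and u1 are the same in both phases.

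**Formulas**

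- True saving per patient = d × (R − 1).
- Reported saving = d × [R(1 − u1) − (1 − u0)].
- Reported ÷ true = 1 − (R·u1 − u0)/(R − 1). The value of d cancels.

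The saving is therefore understated only if R·u1 > u0. With equal under-reporting u in both groups the ratio is 1 − u whatever R is, so worse recall after delirium is not needed for some shrinkage. The saving is overstated only if u1 is below u0/R.

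**Example.** R = 2, u0 = 10%, u1 = 30%: true saving 0.10 × 1 = 0.10; reported saving 0.10 × (1.4 − 0.9) = 0.05; ratio 0.50.

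**Reported ÷ true post-discharge saving**

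| u0 | u1 | R = 1.5 | R = 2 | R = 3 |
|---|---|---|---|---|
| 10% | 10% | 0.90 | 0.90 | 0.90 |
| 10% | 20% | 0.60 | 0.70 | 0.75 |
| 10% | 30% | 0.30 | 0.50 | 0.60 |
| 10% | 40% | 0.00 | 0.30 | 0.45 |
| 20% | 10% | 1.10 | 1.00 | 0.95 |
| 10% | 0% | 1.20 | 1.10 | 1.05 |

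The last two rows describe better reporting after delirium, for example because relatives answer more often for those patients. Across the table the reported saving runs from none of the true post-discharge saving to 20% too much.

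**What the error does not reach.** The cost comparison also includes programme cost and care during the hospital stay, neither of which comes from the calls. The economic effect measure, prevented delirium cases, does not come from them either.

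**The case against.** The case on the other side has real weight.

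- **The patients with least capacity are partly dealt with.** Legal incapacity and inability to communicate verbally are exclusions, and Table 1 carries over the original HELP exclusions, which include severe dementia and aphasia. Patients who cannot take part are covered by family. This stands, but it does not reach patients with milder memory problems, whom the entry rule admits, or decline that begins after admission.
- **The calls are well suited to recall.** If evenly spaced, three calls over three months leave about one month each, the questions are short, and a readmission or nursing home stay is hard to forget. This stands for the large events. It helps less for home care, domestic help, informal care and physician visits.
- **The direction is not established.** This stands. The choice of informant may itself depend on delirium, and if relatives report better, the bias can run in HELP's favour.
- **The detail may sit in the full protocol.** A definition of inability, a log of informants and record checks could be there. For that reason their absence from the article is not the point. The point is the rule the article does state, which ties the substitute informant to taking part and not to recall.

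A reader might infer something stronger: that costs are under-reported most after delirium and that most of HELP's saving is lost. The documents do not support this. The Background says only that delirium can lead to cognitive decline, and no section gives recall accuracy by delirium status. Large losses come from setting under-reporting to zero in everyone without delirium. With assumed costs of 8,000 and 5,000, the true saving is 0.10 × 3,000 = 300. If only delirium cases under-report, by 30%, it becomes 0.10 × (5,600 − 5,000) = 60, a loss of 80%. If both groups under-report by 30%, it is 0.10 × (5,600 − 3,500) = 210, a loss of 30%. With u0 = 10% and u1 = 0 it is 0.10 × (8,000 − 4,500) = 350, more than the truth. All of these describe the post-discharge part only, not the total saving.

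**Conclusion.** The point holds as a modest weakness in how one cost component is measured. The protocol article makes patient recall the source for all post-discharge care use, readmissions included, in a population partly selected for memory problems, and its family fallback does not address recall.

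Under-reporting may follow and may be greater after delirium. If it is proportionally equal in both groups, the post-discharge saving shrinks by that proportion. If it is worse after delirium, it shrinks by more. If it is enough better after delirium (u1 below u0/R), the saving is overstated. Size and sign are therefore uncertain, and every figure beyond the 10-point incidence difference is an assumption. Neither a bias against HELP nor the loss of most of its saving can be asserted from the documents. The change is worth making because it replaces recall with a more objective source for one cost item at little expense.

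**What to change.** 1. Take readmissions to the two participating hospitals from their own admission records, in the control and intervention phases alike. Keep the telephone answer for admissions elsewhere and for all other care.
2. Record who answered at each call (patient, family member or both), and add a sensitivity analysis of post-discharge cost by informant.
3. If a family member is added as informant, trigger this only by baseline items already collected (the memory question at entry and the 6-CIT within 36 hours of admission), by the same rule in both phases. Do not use the CAM result as a trigger: that would tie the informant to the outcome HELP is meant to change, so the mix of informants would differ between phases.

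The cost is a small record extraction in two hospitals that must already identify second admissions to apply the exclusion, plus one extra field on the call form. Readmissions elsewhere and community care would still rest on recall, and relatives' reports carry error of their own.
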